### Study protocols

#### Hysteroscopic evaluation

Following perfect preoperative preparation and the provision of signed consent, the hysteroscopy-guided separation of IUAs was performed under general anesthesia 3–7 days after the end of menstruation. During the surgery, the bladder lithotomy position of the patient was taken. A hysteroscopy operating mirror (Storz, Germany) (dimensions: 5.5–7.5 mm) equipped with hysteroscopic direct-vision micro scissors was used; the normal saline perfusion system continued to expand the uterus at a pressure of 120–140 mmHg, and the cervix was expanded by 5.5–7.5 mm. The hysteroscopy was performed with IUA having been scored before surgery. Cooled knife-sharp separation was used in all of the surgeries, with difficult procedures being performed under the guidance of B-scan ultrasonography. The success criteria were to remove scar tissue, preserve normal intima, normal or basically normal morphology of uterine cavity, and clear display of bilateral fallopian tube openings. For severe intrauterine adhesion, B-ultrasound should be used to monitor the thickness of uterine myometrium during operation to prevent uterine perforation.

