Based on the AFS scoring criteria for IUA [15] (Table 1), patients with moderate/severe IUA were randomized into the experimental group (which included the placement of an ECM scaffold [SIS] and a Foley balloon) or the control group (which included the placement of a Foley balloon) at a ratio of 1:1. In the control group, the Foley balloon was placed after surgery, and normal saline was injected into the balloon according to the size of the uterine cavity. When obvious resistance occurred, the saline injection was stopped (normal saline was 3~5 ml); a drainage bag was connected, and the balloon was removed after 5 days (the recommended prevention time of the balloon by experts in China was 5~7 days [5], recommendation level C). To reduce the infection rate among the patients, a 5-day balloon retention time was implemented in combination with the actual situation of our hospital. Antibiotics were used to prevent any infections from occurring after surgery. In the experimental group, the ECM patch was cut into a 2 × 5-cm rectangle. Fold the patch in half along the midpoint line of the short side, then open it, and place the unfilled balloon on the fold line. Cover the other half of the patch on the balloon, wrap it tightly, clamp it with long curved forceps, and place it into the uterine cavity. Other procedures were the same as those in the control group.

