#### Hysteroscopic re-examination

Patients in both the experimental and control groups received a hysteroscopic re-examination 3–7 days after the end of the second menstruation to evaluate the IUA repair. Postoperative HRT was repeated (the same as stated above). According to the evaluation standard for uterine cavity repair, if the second hysteroscopy showed that uterine cavity adhesion had not been recovered (i.e., there was no obvious change between the uterine cavity’s shape and that before separation, based on hysteroscopy), or the adhesion was more serious, full adhesiolysis was performed again, and additional anti-adhesion methods, such as inserting an IUD and replacing estrogen and progesterone for one month, were implemented.

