### Randomization and allocation

Eligible participants will be randomly assigned to the experimental group or the control group in a 1:1 ratio by central randomization performed by an independent statistician from our team. Random numbers are generated by Excel, which will generate a random number table, and the allocation sequence was registered on the Shanghai Shenkang Development Center (https://crip-ec.shdc.org.cn/html/admin/auth/login). According to the random number table, the statistician puts each grouping scheme into an opaque envelope, writes the code on the outside of the envelope, seals it, and gives it to the researcher. Once the hysteroscopic process entered the uterine cavity, the degree of uterine cavity adhesion was evaluated according to AFS. If the uterine cavity was assessed as reflecting moderate or severe uterine cavity adhesion, the itinerant nurse opened the envelope with the corresponding number. Then, the operator intervened according to the grouping scheme in the envelope. The process of unpacking the envelope was time consuming but did not affect anesthesia or hysteroscopy. The researchers were made aware of the distribution following the hysteroscopic surgery.

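### Opening the envelope on entry to the cavity, and telling the researchers the allocation after the index surgery, leaves adhesiolysis and second-look scoring open to knowledge of the arm

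*Protocol article*

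**What the plan says.** Randomization and allocation gives the order of events at the index procedure. First comes the score: "Once the hysteroscopic process entered the uterine cavity, the degree of uterine cavity adhesion was evaluated according to AFS". If the adhesions are moderate or severe, "the itinerant nurse opened the envelope with the corresponding number. Then, the operator intervened according to the grouping scheme in the envelope". The section ends on disclosure: "The researchers were made aware of the distribution following the hysteroscopic surgery".

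Hysteroscopic evaluation describes the separation, whose adequacy is judged by the operator: "The success criteria were to remove scar tissue, preserve normal intima, normal or basically normal morphology of uterine cavity", with both tubal openings in view. It then describes the devices: "In the control group, the Foley balloon was placed after surgery". In the experimental group a patch is wrapped round the balloon, and "Other procedures were the same as those in the control group".

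Under Hysteroscopic re-examination, both groups "received a hysteroscopic re-examination 3–7 days after the end of the second menstruation to evaluate the IUA repair". The Abstract puts this after 2 months of hormone therapy. Primary outcome measures defines effective repair as a drop of 4 or more in total AFS score, alongside response categories judged by hysteroscopic appearance. Experimental design calls the trial single-blind, and Adverse events refers to breaching the blind. Neither section says who is blinded.

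**The concern.** Two stated rules expose the trial to knowledge of the arm at points where it could be avoided.

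- **During adhesiolysis.** How thoroughly the adhesions are separated is the main co-intervention, and its adequacy is the operator's judgement. An operator who knows which device will follow can, without intending it, separate more or less thoroughly by arm (performance bias).
- **At the second look.** The primary endpoint is a threshold on a score with two visually judged items. A scorer who knows the arm can move borderline cases across the threshold (detection bias).

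Analysis cannot remove either bias afterwards. At stake is whether a difference in response rate can be attributed to the scaffold.

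**Working it through.** The article gives no figure for this point, so the main check sets its statements in time order.

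| Step | Event | Section | Allocation known? |
|---|---|---|---|
| 1 | Cavity entered, baseline AFS scored | Randomization and allocation | No |
| 2 | Envelope opened if moderate or severe | Randomization and allocation | From here |
| 3 | Adhesions separated | Hysteroscopic evaluation | Yes, by inference |
| 4 | Balloon placed, with or without patch | Hysteroscopic evaluation | Yes, unavoidable for the operator |
| 5 | Researchers told the allocation | Randomization and allocation | Yes, stated |
| 6 | Second look, about two months later | Hysteroscopic re-examination; Abstract | Not excluded |

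The allocation is first needed at step 4 but is available from step 2. Step 3 is placed after step 2 because opening follows directly on scoring at entry, and the operator intervenes only then. Step 5 is read as following the index operation, because the second procedure is called a re-examination.

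**Weight of the visual items (Table 1).** Extent and type of adhesion each score 1, 2 or 4, so together they carry up to 8 of the 12 points. One borderline call between the upper two levels moves the total by 4 − 2 = 2 points, half the 4-point responder threshold. Menstrual pattern (0, 2 or 4) comes from the patient's history.

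**Illustration of sensitivity.** From Sample size: n = 83 per arm, one-sided 0.025 (critical value 1.96), and control repair rates of 47% to 71.67%. Assumed here: no true effect, a true response rate p = 0.60 in both arms, and a share u of scaffold-arm non-responders scored as responders.

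- Observed scaffold rate: p1 = p + (1 − p)u; difference d = p1 − p.
- With p̄ = (p + p1)/2: SE0 = √[2p̄(1 − p̄)/n] and SE1 = √[(p(1 − p) + p1(1 − p1))/n].
- Probability of a positive result = Φ[(d − 1.96·SE0)/SE1].

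| u | p1 | d | SE0 | SE1 | Argument of Φ | Result |
|---|---|---|---|---|---|---|
| 0.10 | 0.64 | 0.04 | 0.0754 | 0.0753 | −1.43 | 7.6% |
| 0.20 | 0.68 | 0.08 | 0.0745 | 0.0743 | −0.89 | 18.7% |
| 0.30 | 0.72 | 0.12 | 0.0735 | 0.0729 | −0.33 | 37.0% |

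In patient numbers, u = 0.10 means 0.40 × 0.10 × 83 ≈ 3 upgraded patients.

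Over the article's range of control rates, u = 0.10 gives 6.1% (p = 0.7167) to 10.0% (p = 0.47), and u = 0.20 gives 13.0% to 27.6%.

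**The case against.** Several stronger readings are tempting, and the article does not support them.

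- **That the article states the envelope is opened before adhesiolysis.** It does not name adhesiolysis at that point. The only act that depends on the grouping is device placement, and that comes after surgery. The sequence is the natural reading, but it is an inference, and the performance-bias half of the point rests on it.
- **That the same team scores the second look with the arm known.** The article does not say who performs or scores it, and does not equate the researchers with the scorers. A fuller protocol may name an assessor. What stands is that the article positively states a disclosure and sets no limit on it. The point is therefore more than a missing detail.
- **That the whole primary endpoint is unprotected.** The baseline AFS is scored before that patient's envelope is opened, so the starting value of the change score is safe. The menstrual item has some protection if the patient is the blinded party, which is usual but not stated. The exposure lies in the second-look extent and type items.
- **That the false-positive figures measure the bias.** The upgrade shares have no anchor in the article. They show sensitivity only, and they concern scoring; they say nothing about the size of any performance bias.
- **That the histology is affected too.** It is not part of the primary endpoint, and the article does not say that slides are read with the arm known.

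A fair further objection is that the operator cannot be blinded to the device. That is true, but neither change below requires it.

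**Conclusion.** The concern holds in a limited form. As written, the sequence makes the allocation available before it is needed, and on the natural reading this is before adhesiolysis. The disclosure rule then releases it to the researchers about two months before the primary endpoint is scored, with nothing to keep it from the scorer. The single-blind label does not by itself protect the visually judged items.

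The size of any bias is unknown. With no true effect, 60% response and 83 per arm, upgrading 10%, 20% or 30% of scaffold-arm non-responders would raise the nominal 2.5% to about 8%, 19% or 37%. At 10%, the result is about 6% to 10% for true response rates of 71.67% to 47%. The conclusion rests on two inferences: that the operator's intervention after opening includes adhesiolysis, and that the second-look scorer may be among the researchers who are told.

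**What to change.** Amend Randomization and allocation in two places.

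1. Open the envelope only after adhesiolysis is finished, and after the baseline AFS and the success criteria under Hysteroscopic evaluation have been recorded.
2. Replace the disclosure sentence with a rule that the allocation is withheld from whoever scores the second look until that AFS is locked in the CRIP system. Where existing staffing allows, the scorer should be a team hysteroscopist who was not at the index procedure.

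The cost is amendment wording, a changed theatre routine, a rota constraint for the second look, and a short wait for the envelope at the end of surgery. The article says that opening the envelope takes time but did not disturb anaesthesia or hysteroscopy, so moving it looks feasible. Staffing is not described, so it cannot be promised that the second change needs no additional person.

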##### No response

No significant changes were observed in the endometrial cavity under hysteroscopy compared with before separation.

The response rate % = the number of participants with successful intrauterine repair in a group / the number of subjects in that group × 100%.

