### Sample size

The sample size calculation is based on the repair rate of moderate/severe IUA. Based on the fact that the repair rate of Foley balloon placement was 47–71.67% [8, 19], we assume that the effective rate of uterine adhesion repair can reach 80%. According to the calculation method for several cases related to the superiority study, the number of samples was estimated as 83, with *α* = 0.025 (one-sided) and *β* = 0.2. A sample size of 83 prospectively enrolled participants in each randomization arm. In consideration of a dropout rate of 20%, we will enroll 100 participants in each group response.

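### The withdrawal list lets investigators who know the arm take women out of the study before the primary assessment, so primary outcomes can be lost in an arm-dependent way

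*Protocol article*

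**What the plan says.** **When the arm becomes known.** Under Randomization and allocation, the envelope is opened during the first hysteroscopy, once adhesions have been graded moderate or severe. "Then, the operator intervened according to the grouping scheme in the envelope". The section ends: "The researchers were made aware of the distribution following the hysteroscopic surgery".

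**When the primary outcome is measured.** Under Hysteroscopic re-examination, both groups "received a hysteroscopic re-examination 3–7 days after the end of the second menstruation to evaluate the IUA repair". The abstract puts this after two months of hormone therapy.

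**Who may be withdrawn.** The withdrawal criteria (the list after the exclusion criteria) include breach of the eligibility criteria, other unexplained serious complications, pregnancy during treatment, and an investigator's opinion that the woman is not suitable to take part. Only the pregnancy item carries any reference to time.

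**What is counted.** The response rate defined under Primary outcome measures divides successful repairs by "the number of subjects in that group × 100" (per cent). It does not say whether a withdrawn woman stays in that number.

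**How losses enter the sample size.** Under Sample size, 83 per arm are required, and "In consideration of a dropout rate of 20%, we will enroll 100 participants in each group".

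**The concern.** Randomisation protects the comparison only if what happens to a woman's data afterwards does not depend on her arm. Here three grounds for removal can operate after allocation, in the hands of people who know the allocation, before the primary outcome has been observed.

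- Unsuitability has no objective criterion.
- A serious complication may be related to the device that was placed.
- Eligibility facts pre-date the envelope, so a violation found later is no reason to lose the outcome. Whether anyone looks for one may depend on how the woman is doing.

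At stake is the primary repair rate. If the women removed from one arm differ in prognosis from those removed from the other, the arms that remain are no longer comparable. A missing second look cannot be restored at the analysis stage; it can only be imputed under assumptions.

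**Working it through.** **1. Does the list operate after allocation?** The pregnancy item refers to the treatment period, so at least part of the list applies after the envelope. The eligibility, complication and unsuitability items carry no limit to the time before it.

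**2. Is the arm known by then?** Yes. The operator knows it in theatre and the researchers know it after that surgery. The second look comes after the second menstruation, so about two months pass with the arm known and the primary outcome unmeasured.

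**3. The plan's own figure.** 83 × 1.2 = 99.6, rounded up to 100 per arm, which reproduces the stated enrolment. The plan therefore works if 100 − 83 = 17 women per arm contribute no primary outcome.

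**4. Does the sample size suggest that women who leave are not counted?** The protocol plans for 80% repair with the scaffold but gives only a range, 47% to 71.67%, for the balloon. Assume 60% for the balloon: the pooled two-proportion formula at one-sided 0.025 and 80% power then gives 82, close to the stated 83. On that assumption, with power = Φ[(Δ − 1.96·SE₀)/SE₁]:

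- *83 evaluable per arm, 60% v 80%.* SE₀ = √(2 × 0.70 × 0.30/83) = 0.0711 and SE₁ = √[(0.24 + 0.16)/83] = 0.0694. Power = Φ[(0.20 − 0.1394)/0.0694] = Φ(0.87) ≈ 0.81.
- *100 per arm, with 20% lost in each arm and counted as not repaired.* The rates become 0.8 × 60% = 48% and 0.8 × 80% = 64%. SE₀ = √(2 × 0.56 × 0.44/100) = 0.0702 and SE₁ = √[(0.2496 + 0.2304)/100] = 0.0693. Power = Φ[(0.16 − 0.1376)/0.0693] = Φ(0.32) ≈ 0.63.

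The numbers fit an analysis of women with an outcome better than one that counts losses as failures. This supports an inference about the analysed set; it does not prove it.

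**5. What could arm-dependent loss do?** Assume 100 women per arm and no true difference. Ten women leave the scaffold arm only and are dropped from its denominator.

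| True repair in both arms | Who leaves the scaffold arm | Scaffold rate shown | Control rate | Apparent difference |
|---|---|---|---|---|
| 60% | 10 non-responders | 60/90 = 66.7% | 60% | +6.7 points |
| 60% | 10 at random (6 responders, 4 not) | 54/90 = 60.0% | 60% | 0 |
| 60% | 10 responders | 50/90 = 55.6% | 60% | −4.4 points |
| 47% | 10 non-responders | 47/90 = 52.2% | 47% | +5.2 points |
| 71.67% | 10 non-responders | 71.67/90 = 79.6% | 71.67% | +8.0 points |

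The 47% and 71.67% rows use the ends of the protocol's own balloon range. The number leaving and the selection are assumptions. For the 66.7% v 60% case the uncorrected chi-square test gives p = 0.34: the estimate shifts, but this loss alone does not produce a significant result.

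**The case against.** The strongest case on the other side has five parts.

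*The link to the primary analysis is inferred.* Correct. The sample-size text speaks only of dropout, and plans that analyse all randomised women also inflate for missing outcomes. The response-rate denominator can be read as everyone allocated. A reader might infer that the protocol excludes withdrawn women from analysis; it does not say so. The loss of the outcome itself does not depend on that reading.

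*Analysis sets belong in the SAP.* Also correct, and the absence of an intention-to-treat statement is not the point here. The point is a stated rule that ends participation before the outcome is measured.

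*Investigators cannot pick out non-responders before the second look.* Largely right. Two of the three AFS components, extent and type of adhesion, need hysteroscopy; only the menstrual component shows earlier. The illustration with ten non-responders is therefore close to a worst case for that number leaving. A reader might go further and infer that the 20% allowance is enough to manufacture significance: 20 non-responders leave the scaffold arm and 20 women leave control at random, giving 60/80 v 48/80. That needs near-perfect foresight. Even then p is 0.043 without continuity correction and 0.063 with it. It should not be used as evidence.

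*Harm is recorded anyway.* A reader might infer that withdrawing women with complications under-counts harm. The Adverse events section has all events during the study evaluated and recorded, with reporting deadlines for serious ones, so the event that triggers withdrawal should already be captured. That inference is not supported.

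*Eligibility is checked beforehand.* Screening precedes surgery, eligible women are the ones randomised, and the envelope waits for AFS grading. A further check before the envelope would be largely redundant, and the eligibility item may be meant for screened women. The text does not confine it to them.

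**Conclusion.** The concern holds as a defect in a stated rule. Investigators who know the arm may end a woman's participation on open-ended or device-related grounds before her primary outcome is observed, so outcomes can be lost in an arm-dependent way. The conclusion rests on three things in the text: the withdrawal list without a time limit, knowledge of the arm from the first surgery, and a later primary assessment. It does not rest on any assumption about numbers.

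The size and direction of the bias are unknown. The shift of 6.7 points is an illustration under assumed 60% repair in both arms and one-sided loss of ten non-responders, and loss of responders would push the other way. That the 20% dropout allowance covers these women is a reasonable inference, not something the protocol states.

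**What to change.** In the withdrawal criteria, separate stopping study treatment from leaving the study. Clinical decisions on treatment stay as they are. Then state that:

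1. once the envelope is opened, neither an investigator's view that a woman is unsuitable nor an eligibility violation found later ends her follow-up;
2. women with serious complications remain in follow-up, including the second-look assessment where they agree;
3. every woman whose envelope was opened is counted in her assigned arm in the denominator of the response rate;
4. withdrawals are reported by arm and reason.

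The cost is a rewording of the list and one clarifying sentence at the response-rate formula. A few more women must be followed to the second look, and keeping ineligible women may dilute the effect slightly. If second looks are still missed and counted as not repaired, power falls; the 0.63 in the working is the figure for 20% lost in each arm under the assumed rates. Keeping women in follow-up is what limits that loss.

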### Outcome measures

#### Primary outcome measures

The response rate of the repair of moderate/severe IUAs served as the main evaluation index.

The definition of an “effective repair of IUA” was considered as the total AFS of adhesion having been decreased by ≥4 points.

##### Complete response

The morphology of the endometrial cavity was returned to normal, and there was complete endometrial coverage.

##### Moderate response

The endometrial cavity reflected a normal morphology, the endometrial volume was enlarged compared with before surgery, and the IUA score was decreased by 1–2 grades, although a small amount of adhesion remained.

##### No response

No significant changes were observed in the endometrial cavity under hysteroscopy compared with before separation.

The response rate % = the number of participants with successful intrauterine repair in a group / the number of subjects in that group × 100%.

### Secondary outcome measures

These included the endometrial thickness, menstrual volume, and clinical pregnancy rate.“Endometrial thickness” referred to the anterior and posterior diameter of the endometrium in the longitudinal section of the uterus, which changed with the menstrual cycle. The measurement of endometrial thickness was based on the following: In the median sagittal section of the uterine body, perpendicular to the midline of the endometrium, the maximum thickness diameter was measured between the lateral edges of the double-layer endometrium. If there was uterine effusion, the thickness and diameter of the two monolayers were measured and added to the overall total.The evaluation of menstrual volume is the total amount of bleeding in each menstrual cycle. The normal menstrual volume is 20–60 ml, and more than 80 ml is considered to be excessive. Typically, this is judged by the number of sanitary napkins used. Under normal circumstances, 10–20 sanitary napkins will be used in a menstrual cycle. If the level of menstruation required fewer than 10 sanitary napkins or only one was needed, the amount of menstruation had been reduced. Based on the number of sanitary napkins that were used before the hysteroscopy, if this was more than the amount before the procedure, the amount of menstruation was considered to have increased. If there was no change in the menstrual volume compared with before the procedure, the menstrual volume was considered as having shown no improvement.Blood β-hCG and progesterone were measured 14 days after embryo transfer to evaluate whether a biochemical pregnancy was present. On day 35 after embryo transfer, a vaginal ultrasound showed that there was a gestational sac in the uterus with an embryo and fetal heart beat; this was determined as a clinical pregnancy.Ongoing pregnancy rate = the number of clinical pregnancies ≥12 weeks/the number of embryo transfer cycles × 100%Clinical pregnancy rate = the number of clinical pregnancies/the number of embryo transfer cycles × 100%Embryo implantation rate = the total number of implanted embryos/the total number of transplanted embryos × 100%Ectopic pregnancy rate = the number of ectopic pregnancies/the total number of clinical pregnancies × 100%Early spontaneous abortion rate = the number of spontaneous abortions at a gestational age of <12 weeks/the total number of clinical pregnancies × 100%

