Endometrial injury can easily cause IUA, which primarily manifests as an endometrial basal layer injury caused by trauma, infection, and other factors, resulting in the dysfunction of functional endometrial repair; in turn, this will lead to the proliferation of fibrous connective tissue and endometrial fibrosis as well as partial or total intrauterine occlusion [2, 4]. According to the consensus of Chinese experts on the clinical diagnosis and treatment of intrauterine adhesions [5], at present, for patients suffering from infertility, recurrent abortion, and oligomenorrhea and for those with special fertility requirements, transcervical resection of adhesion (TCRA) can be conducted as a preferred treatment (recommendation level: C). Moreover, TCRA combined with an intrauterine device (IUD), Foley balloon support, or estrogen and progesterone replacement therapy has shown degrees of anti-adhesion value, although their effects are variable. An IUD placement after moderate and severe IUA could reduce the formation rate of re-adhesion to 35% [6] (evidence level: I). But meta-analysis showed that the menstrual improvement rate ranged between 28.5 and 100%. Several studies have indicated significant differences in this regard [7]. In addition, although an intrauterine balloon can make the total effective rate of IUA repair reach 71.67% [8] and improve the menstrual rate up to 81.4–95% [9, 10], the shape of the balloon used in clinics is not suitable for the intrauterine cavity, which makes it difficult to block the wound completely. Moreover, if the intrauterine balloon is not placed properly, intimal ischemia and necrosis may occur, which will impact intimal regeneration and repair. In particular, for patients with severe IUA, due to endometrial basal layer damage, reduced residual normal endometrial tissue, and poor regeneration ability, the recurrence rate of postoperative adhesion can still be as high as 62.5%, while the success rate of pregnancy will range between only 22.5 and 33.3% [11]. Therefore, establishing an anti-adhesion method that can promote the repair of endometrial injury is of great significance.

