### Evaluation criteria

The evaluation criteria for inclusion in the protocol were as follows.Secondary hypomenorrhea: The menstrual blood volume was less than 20 ml or had decreased by 1/3 of the original menstrual blood volume, and the menstrual cycle length was less than 3 days if the previous menstrual bleeding duration and volume had been normal. Patients could calculate this according to the number of sanitary napkins they had used.Diagnosis of infertility: Patients who failed to become pregnant successfully with a normal sex life without taking contraceptive measures for more than 1 year.A “thin endometrium” meant that the thickness of the endometrium was less than the threshold thickness for becoming pregnant. Currently, there is no unified standard for this threshold. Most scholars posit that an endometrial thickness of <7 mm as measured by transvaginal ultrasound on the day of human chorionic gonadotropin (hCG) could be considered a thin endometrium [16].An IUA diagnosis under 3D ultrasound [17] in which type I indicates a clear endometrium and a discontinuous endometrial line, type II denotes a mild intrauterine separation with a separation diameter less than 1 cm, type III refers to an unclear endometrium with a thickness of less than 0.2 cm that is not demarcated from the surrounding muscle layer, and type IV involves severe intrauterine separation with a separation diameter greater than 1 cm. A diagnosis could be made if one of the above characteristics was present.“Repeated embryo implantation failure” refers to failure to achieve a pregnancy following 2–6 IVF cycles, in which more than 10 high-grade embryos were transferred into the uterus [18].

The protocol complies with the principles of the Declaration of Helsinki as well as Good Clinical Practice (GCP) guidelines. The hospital’s ethics committee approved the study protocol. The trial was registered in the Chinese Clinical Trial Registry.

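### Menstrual volume is classed by any rise in napkin count, with no minimum and unclear cycles; comparing the arms on that class would lose power for a modest difference

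*Protocol article*

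**What the plan says.** The outcome list under Secondary outcome measures reads: "These included the endometrial thickness, menstrual volume, and clinical pregnancy rate". Menstrual volume is total bleeding per cycle, and "Typically, this is judged by the number of sanitary napkins used".

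The comparison rule opens "Based on the number of sanitary napkins that were used before the hysteroscopy" and continues "if this was more than the amount before the procedure, the amount of menstruation was considered to have increased". The other class is: "If there was no change in the menstrual volume compared with before the procedure, the menstrual volume was considered as having shown no improvement". A decrease is given no class.

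Two size thresholds appear elsewhere, and the comparison rule uses neither:
- The same section has a fixed cut-off: "If the level of menstruation required fewer than 10 sanitary napkins or only one was needed, the amount of menstruation had been reduced".
- Evaluation criteria defines secondary hypomenorrhea at entry by size: "The menstrual blood volume was less than 20 ml or had decreased by 1/3 of the original menstrual blood volume".

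Statistical analysis methods provides a t-test for measurement data, a rank-sum test for ordinal categories and a chi-square test for nominal categories. It does not say which of these applies to menstrual volume.

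**The concern.** There are two separate problems.

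**Wording.** Read literally, both sides of the comparison lie before treatment, and no postoperative menstruation is named. The first operation and the re-examination are both hysteroscopies, so a reader cannot be certain which one is meant.

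**Information.** One extra napkin counts as increased, whether it reflects treatment or ordinary variation between cycles. A woman who goes from 3 to 4 napkins is increased under one sentence and still reduced under another. Both arms have adhesiolysis, a balloon and hormone cycles, so the count may rise in many women in both arms. The more controls who are classed as increased, the less room a yes/no class leaves for the scaffold to show a further gain.

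What is at stake is the chance of detecting a modest benefit on a named secondary outcome.

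**Working it through.** **The plan's own figure.** There is no power or sample size for menstrual volume. The 83 per arm in Sample size concerns the repair rate. It is roughly reproduced by taking 80% against an assumed control rate of 60%, inside the article's 47–71.67%: [1.96√(2×0.7×0.3) + 0.842√(0.6×0.4 + 0.8×0.2)]² / 0.20² = 81.2, so 82 per arm. I use 83 per arm below.

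**Assumed inputs, none of them in the documents.** Napkin count per cycle: mean 6, SD 2, before–after correlation 0.6, whole numbers. True arm difference 0.75 napkin. Rise common to both arms 0, 1 or 2. Tests two-sided at 0.05, as in Statistical analysis methods.

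**SD of the change.** 2√(2(1−0.6)) = 1.79. Rounding two counts adds variance 2/12, giving √(3.20+0.17) = 1.83.

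**Share classed as increased.** A whole-number rise of at least 1 has probability of about Φ((mean change − 0.5)/1.83).

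| Common rise | Control | Experimental | Power of chi-square on the class |
|---|---|---|---|
| 0 | Φ(−0.27) = 39% | Φ(0.14) = 55% | about 56–58% |
| 1 | Φ(0.27) = 61% | Φ(0.68) = 75% | about 53–54% |
| 2 | Φ(0.82) = 79–80% | Φ(1.23) = 89% | about 40–41% |

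The power ranges are the spread across repeated simulations of 3,000 to 4,000 trials per setting. So 39% of women with no true change are classed as increased.

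**Same data, size of the change kept.**
- Change in count: SE = 1.83√(2/83) = 0.28; 0.75/0.28 ≈ 2.63; power Φ(2.63−1.96) ≈ 75%.
- Postoperative count adjusted for the preoperative count: residual SD is 2√(1−0.36) = 1.60, or about 1.63 with rounding; SE = 0.25; 0.75/0.254 ≈ 2.96; power Φ(2.96−1.96) ≈ 84%. Simulation gives about 83%.
- Rank test of the change, by simulation: about 73%.

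Of the roughly 25 points between the class and the adjusted count at no common rise, about 8 come from the covariate. The rest comes from keeping the size of the change.

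**Range.**
- SD 4, same difference: about 20% for the class against 33% for the adjusted count.
- Difference 1.5 napkins: 99% (no common rise) or 88% (common rise 2) for the class, against about 100%.
- No arm difference: type I error about 5% for every method.

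**A check that needs no mean or SD of the count.** Take a normally distributed change and the arm difference that gives a comparison of mean change 80% power: (1.96+0.842)√(2/83) = 0.435 SD. Cut at any increase:
- If 50% of controls increase, the classes are 50% against Φ(0.435) = 66.8%. Power is 60%, and 134 per arm would be needed to regain 80%.
- If 81.4% of controls increase, power is 42%. If 95% increase, it is 20%.

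The last two rates come from the balloon figures in Background ("improve the menstrual rate up to 81.4–95"). The definition of improvement behind them is not shown, so they are only a proxy for this trial's control arm.

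**The case against.** **The wording is a slip.** This largely stands. The no-change sentence shows that a later count is set against a pre-procedure baseline. Hysteroscopic re-examination is scheduled after the second menstruation, which gives a coherent reading of the two phrases. A reader might infer that the plan compares two pretreatment counts, but the documents do not support that. The slip also does not cause the power loss, which comes from the cut.

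**No test is assigned.** This also stands. The article gives no menstrual improvement-rate formula and does not say that the class is tested by chi-square; an analysis of the counts would avoid the loss. A reader might infer that the count is certain to be discarded, and the text does not go that far. Still, any increase versus no change is the only comparison rule stated for this outcome, and nothing says that the size of the change is used. The point concerns a rule the article states, not detail it leaves to an analysis plan.

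**The inputs are assumed.** True. The loss is small for a large effect, and with SD 4 neither analysis has useful power.

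**Saturation is not shown.** Fair. Background also cites a menstrual improvement range of 28.5–100% from a meta-analysis, so the control rate is unknown.

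**Chance increases fall on both arms alike.** Correct, and so type I error is unaffected. A reader might take the 39% as a bias in favour of the scaffold; it is not. Symmetry does not prevent dilution of a real difference.

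**Conclusion.** The point holds conditionally. The stated rule has no minimum increase, gives no class to a decrease and does not clearly name the postoperative cycle. If the arms are compared on that class, power for a modest difference is materially lower than with the counts: about 40–58% against about 75% (change) or 83% (adjusted), under assumed mean 6, SD 2, correlation 0.6, 83 per arm and 0.75 napkin. The gap narrows to 20% against 33% at SD 4, and to 88–99% against about 100% for a 1.5-napkin difference. The direction was the same in every setting with a true difference that was tried; the size depends on inputs that the documents do not give.

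The documents do not support a stronger claim of biased results, a certain loss of power or a damaged trial. The outcome is secondary, and the primary outcome and sample size do not rest on it. Correcting this is worthwhile because it is cheap.

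**What to change.** 1. Name both menstruations: the last before the first operation and the last before the second-look hysteroscopy. The second choice matters because women whose adhesions had not recovered at that examination receive further adhesiolysis and other measures, so a later cycle would partly reflect treatment given for failure.
2. Compare the postoperative napkin count between arms by linear regression with the preoperative count as covariate, reporting the adjusted mean difference with its 95% confidence interval. A rank-sum test of the change is an acceptable alternative if the counts are badly skewed.
3. Report increased, unchanged and decreased by arm as description only.

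**Cost.** A rewritten sentence and one regression. The rule already relies on counts before and after, so no new measurement is needed. The downside is that a mean difference in napkins is less familiar to clinicians than a percentage improved, which the descriptive table can still show.
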